### d. Inclusion criteria

All medically stable twin infants admitted to the NICU of the IWK Health Centre and St. Justine Hospital will be eligible for the study. Twins will be deemed to be medically stable if they are:

a. Free from infection, and

b. Breathing room air or receiving oxygen via nasal prongs.

Twins may be receiving feeds via gavage tubes, IV therapy via peripheral or central line, and may be experiencing periods of apnea.

Additionally, parents of the twins must understand written and spoken English or French.

### e. Selection criteria for study subjects

The parent (s) of twin pairs who meet the inclusion criteria will be approached by the study investigator/nurse and informed of the study. Signed written informed consent will be obtained before recruitment into the study.

### f. Exclusion criteria

Twin infants to be excluded are those who at the time of study entry:

i. Weigh less than 1000 grams;

ii. Are receiving mechanical ventilator support;

iii. Have chest tubes or umbilical catheter in situ;

iv. Have major congenital anomalies or chromosomal aberrations;

v. Only one of the twin pair requires overhead phototherapy;

### g. Allocation of participants to the trial groups

see Figure 1

**Figure 1 F1:**
[figure not shown]
**Allocation of participants to study groups**.

### h. Randomization

Eligible infants whose parent(s) have provided consent will be randomized by a computerized website accessed by the principal investigator or research nurse. Allocation concealment will be ensured using randomly permuted blocks of two, four or six. Infants less than or equal to 31 6/7 weeks will be randomized separately from those twins greater than or equal to 32 weeks. Infants from different study sites will also be randomized separately to ensure identical proportions within the co-bedding and standard care groups.

## What are the proposed methods of protecting against sources of bias?

Due to the unblinded nature of the intervention, it is important to strictly adhere to rigorous methods to eliminate potential bias. The use of an off-site computerized website for group allocation will decrease the risk of allocation bias. The individuals coding pain response will be blinded to the twins treatment status (whether co-bedding or receiving standard care). The video camera will be set up to focus only on the infant's face and will be controlled by the investigator or research nurse. Coding of pain scores will be calculated using the Premature Infant Pain Profile (PIPP) [72]. The PIPP is considered a reliable and valid tool to measure procedural pain in both preterm and term neonates [73-75]. Both composite PIPP scores and combined behavioral (facial) indicators will be reported in each group. Coding will be carried out at McGill University at [name] lab by 2 coders (coder A and coder B). Each coder will only code data on infants who are co-bedding (A) or code data on infants who are receiving standard care (B). Coders will not enter the unit, communicate with each other or compare data sets (i.e. PIPP scores will be estimated without knowledge of group assignment). The use of different coders (who have no previous knowledge of patient enrolment and randomization to code separately for infant facial responses, etc and who will remain blinded to each other's assessments), is expected to minimize observer bias. Research coders A and B will be trained separately by the principal investigator and a member of [name] research lab team. Training will be standarized and coding performances assessed so that an interclass coeffecient (ICC) of 0.85 is reached between the coders' standarized scores. Following the initial training, coders will be retested quarterly using standarized videotapes to ensure inter-rater reliability. If the ICC drops below 0.75, re-training and re-coding will take place. This reliability check conducted with standarized tools will minimize the likelihood of observer bias. Every three months, coders A & B will also re-code two randomly selected videotapes from the first weeks of coding to ensure intra-rater reliability. ICC's of 0.75 will be considered the cutoff point of acceptability. Following study completion, previously assigned group coders will be asked to code a random selection of approximately 20% (n = 6) of the tapes from the alternate group. Inter-rater scores will be correlated to ensure that if differences are found between the groups, these differences are related to the intervention of co-bedding and not to systematic error between the two coders scoring techniques.

In addition, every attempt will be made to assign the same nurse to care for a set of twin pairs regardless of which group they have been assigned. Adherence to this aspect of the study protocol will be recorded daily until the study heelstick has been completed.

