## What is the intervention and proposed duration of treatment?

### a. Co-bedding care

Following randomization to the co-bedding group, twin infants will be placed together in a Giraffe Incubator or crib lying side-by-side. Twins will be diaper clad and nested together in boundaries consistent with neonatal care practices. Larger infants may be partially clothed if in an open crib but still able to freely touch one another and remain nested together. Twins will be positioned close to each other (lying face-to-face, back-to-back, or in spooning positions), permitting contact between them. All infants will have cardio-respiratory monitoring while co-bedding. One side of the incubator/crib will be for twin 'a' and one side will be for twin 'b' and infants and their equipment will be colour coded. Incubator temperatures will be determined using clinical reasoning, anticipated neutral thermal environmental needs (based on infant weight, gestational and post natal age) and incubator settings prior to initiation of co-bedding. If servo temperature regulation is required, most likely in the case of younger twin pairs or discordance in infant weights, the servo probe will be placed on the larger infant. Infant temperatures will be closely monitored and recorded throughout the co-bedding condition to maintain normal axilla readings between 36.8 and 37.2 degrees Centigrade.

All infants will be co-bedded for no less than 24 hours prior to heelstick to allow for stabilization following transfer. The heelstick being studied will occur no greater than 10 days following initiation of co-bedding. Duration of co-bedding will be recorded and controlled for in the analysis if necessary. Limiting the length of co-bedding duration decreases the degree of variance possible for this variable yet still allows adequate time for a heelstick to be ordered as part of usual care.

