The medically indicated heelstick will be performed by a designated group of experienced nurses and lab technicians who have performed heelstick procedures in previous studies in the NICU in a standardized manner according to the institutional and unit policy. The nurse assigned to care for the twin will assist with the heelstick procedure. Their role will be to provide non-pharmacologic measures as per the NICU pain guidelines as they would do normally. None of the members of the research team or nurses conducting heelstick will prompt the bedside nurse to alter their care in any way. All non-pharmacologic strategies for pain relief implemented by the nurse including number of 24% sucrose doses given will be recorded and confirmed with video recorded data.

Infants assigned to the co-bedding group, may continue co-bedding, should their parents choose, up to 48 hours prior to discharge at which time monitors will be disconnected and the infants separated.

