### c. Other outcomes

Clinical stability (incidence of apnea or bradycardia, and need for supplemental oxygen prior, during and following (i.e. recovery period) heelstick, the number of painful procedures experienced by the neonate prior to the heelstick procedure, infection rates, and caregiver error will be compared between the groups.

The measurement of the main variables of the study relies on three strategies: video recording of facial actions, monitoring of cardio-respiratory measures and oxygen saturations, collection of salivary cortisol and chart review (Table 1).

**Table 1 T1:** Key variables, measures proposed, data sources, and time of administration

Variables	Measures	Method/Sources	Time of administration
Pain response	Premature Infant Pain Profile (PIPP)	Videotape of facial responses	Baseline, warming heelstick and recovery

Physiologic recovery	Heart rate, Oxygen saturation	Somté software	Baseline, warming heelstick and recovery

Heart rate variability	Cardiac monitoring	Somté software	Baseline, warming heelstick and recovery

Hormonal stress response	Cortisol	Sorbette oral swab	Prior to heelstick (basal) and 20 minutes after (stress) the heel stick

Frequency of 24% sucrose administration	Count	Chart medication record, confirmed with videotape recording	2 minute prior and during intervention

Co-twin Response	All measures identical to the twin undergoing heelstick, except sucrose count	Identical measures, except sucrose count	Baseline, warming heelstick and recovery

Safety surveillance	Caregiver error Infection rate	Institutional adverse event and infection control surveillance	Quarterly

Clinical Stability	Supplemental oxygen Incidence of apnea Bradycardia	Chart review	Baseline, warming heelstick and recovery

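### Face-only camera framing may not secure the coder blinding that the protocol promises for the facial part of the primary PIPP score

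*Protocol article*

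**What the plan says.** The protocol's section on protecting against bias accepts that the intervention is open and relies on blinded coding of the tapes: "The individuals coding pain response will be blinded to the twins treatment status (whether co-bedding or receiving standard care"). The safeguard on the picture itself is this: "The video camera will be set up to focus only on the infant's face and will be controlled by the investigator or research nurse". The other coder safeguards limit what coders are told. They work at a university laboratory, stay out of the unit, have no contact with each other, and know nothing of enrolment or allocation. The analysis section adds that the coders' blinding lasts until the analysis is finished.

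The section on co-bedding care sets the conditions under which those infants are filmed: "Twins will be positioned close to each other (lying face-to-face, back-to-back, or in spooning positions), permitting contact between them". In the sentence that gives each twin a side of the bed, it adds that "infants and their equipment will be colour coded". The standard care section does not mention colour coding. The co-bedding section also says that all the nurse's non-drug comfort measures, "including number of 24% sucrose doses given will be recorded and confirmed with video recorded data".

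Table 1 gives the source of the PIPP as "Videotape of facial responses", with heart rate and oxygen saturation taken from monitoring software.

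**The concern.** Facial coding is the part of the primary outcome that rests on human judgement, and blinded coding is the protocol's main defence against expectation in an open trial. A coder who sees a second infant beside the filmed face knows that the tape comes from the co-bedding arm. In a trial about whether a twin gives comfort, that knowledge could lower the score.

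The planned reliability checks would not expose this. Training and quarterly testing use standardized tapes. In the final check each coder will "code a random selection of approximately 20% (n = 6) of the tapes from the alternate group", but the second coder would see the same cues as the first, so good agreement would not show that the blind held.

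**Working it through.** Whether the arm is visible cannot be calculated, so the main check sets the sections side by side.

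1. **Who frames the shot.** The investigator or research nurse does. The randomization section gives the same roles access to the allocation website, and they will see whether the twins share a bed. The framing is therefore done by unblinded staff.
2. **What lies near the face.** In two of the three listed positions, face-to-face and spooning, the sibling's head or hand can lie close to the filmed face. Back-to-back makes this less likely.
3. **Colour codes.** They are described for co-bedding only, and the text does not say where they are placed. The inclusion criteria allow nasal prongs and gavage tubes, which could be in a facial shot. Whether those items carry a colour is not stated.
4. **Second use of the video.** A tight facial shot might show sucrose being given. The literature review lists swaddling and facilitated tucking among comfort measures, and these act on the body. Confirming all such measures on video needs either a wider frame than the bias section describes or a second recording that the article does not mention.
5. **Both twins recorded.** The follow-up section collects data on both infants at the same time, and Table 1 gives the co-twin nearly identical measures. In the co-bedding arm both infants are in one incubator or crib.

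**Scale, as illustration only.** Inputs from the sample size section: difference 1 point, SD 2.0, two-sided alpha 0.05, power 80%, 128 infants.

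- The plan's own figure: n per arm = 2 × (1.960 + 0.842)² × 2.0² / 1² = 62.8, so 63. The t-test version gives 63.8, so 64 per arm and 128 in total. The stated size is reproduced, with infants treated as independent.
- Standard error of the difference: 2.0 × √(2/64) = 0.354.
- With no true effect and a systematic scoring shift s between arms, the false-positive rate is 1 − Φ(1.96 − s/0.354) + Φ(−1.96 − s/0.354).

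| Assumed shift s (points) | False-positive rate |
|---|---|
| 0 | 5.0% |
| 0.25 | 10.9% |
| 0.5 | 29.3% |
| 0.75 | 56.4% |
| 1.0 | 80.7% |

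The average shift is the share of co-bedding tapes with a visible cue times the shift on those tapes. If 30% of tapes show a cue worth 0.5 point, it is 0.3 × 0.5 = 0.15 point. If 50% show a cue worth 1 point, it is 0.5 × 1 = 0.5 point. All of these shares and shifts are assumptions. Positive correlation within twin pairs, handled by the planned GEE, would widen the standard error and lower the rates in the table somewhat.

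**The case against.** A reader might infer that the blind fails and that the arm can be seen on the tape. The documents do not support this. No section places the sibling, tubing or a colour tag in the frame. Face-only framing is stated precisely to meet this risk, and it can coexist with close positioning. A colour tag reveals the arm only to a coder who knows that colours mark one arm, and nothing says that coders are told. Nor is framing the only safeguard, although it is the only one stated against visual cues.

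Two further limits stand. The PIPP also has physiological components, and heart rate and saturation come from monitors, so expectation can act only on the coded facial part. The scale figures depend wholly on assumed inputs.

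It can also be said that cropping and muting are operating details that a journal article leaves out. That is fair for the details alone. But the article sets out its blinding method at some length, and the method as stated sits uneasily with its own rules on positioning and use of video. That tension remains.

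**Conclusion.** The point holds as a modest, inexpensive improvement: the stated framing may not secure the promised blinding. It rests on the listed positions, on colour coding described for one arm, and on the second use of the video. It does not rest on any evidence that cues are in the frame. The direction of any bias would plausibly favour co-bedding. Its size is unknown, though with a 1-point target even a small systematic shift in facial scoring would matter.

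The coder assignment in the same section is a different flaw: "Each coder will only code data on infants who are co-bedding (A) or code data on infants who are receiving standard care (B"). It confounds coder with arm whatever the tape shows, and masking leaves it in place. It also interacts with the present point, because a coder who notices siblings on a few tapes could infer the arm of all the tapes in that batch.

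**What to change.** - Before tapes go to the coding laboratory, crop or mask every recording in both arms to the index infant's face and remove the sound. Keep an uncropped master so that someone other than the coders can confirm comfort measures and sucrose counts.
- Use the same colour coding in both arms, or keep it off equipment at the face.
- For each tape, have the coder log any visible group cue and guess the arm. Report the results as a check of the blind. The guesses will be easier to interpret if each coder scores tapes from both arms.
- Keep all randomized infants in the primary analysis, and do not rely on an analysis that excludes flagged tapes. Flags would arise almost only in the co-bedding arm, and mostly among infants lying face-to-face or spooning. Dropping them would remove infants from one arm after randomization and conflict with the intention-to-treat principle.

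The cost is a short editing step for at least 128 recordings, and up to 128 × 2 = 256 if a co-twin tape is coded for every heelstick, plus two short items per tape. No change to infant care is needed for the video steps. The coder-by-arm assignment needs its own correction.

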## What are the proposed outcome measures?

### a. Primary outcome

The pain response to heelstick determined by physiological and behavioral reactions to a painful event (Premature Infant Pain Profile (PIPP) scores) will be compared between co-bedding and standard care groups.

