We based our PIPP score assumptions on previous studies which reported PIPP scores of 10.7 (2.3) vs. 12.9 (2.5) from a study on kangaroo skin-to skin care versus incubator care in preterm infants 32-36 weeks of gestational age [61] and PIPP scores 8.9 (*CI *7.9-9.9) versus 10.7 (*CI *9.6-11.8) in preterm infant 28-31 6/7 weeks of gestational age. Based on these reported 0.5 and 0.6 standard deviation pain scores [66] and the reported values in the above studies, we used a conservative standard deviation estimate of 2.0 as our proposed study population will encompass both groups of infants. Sample size was calculated using a 2-sided alpha error of 0.05 and a power of 80 percent. We designed the study to detect a difference of 1 point or greater change (SD 2.0) in the PIPP scores. One hundred and twenty-eight infants would be required to identify this variation in the PIPP scores if such a difference is in fact caused by co-bedding. With this sample size, we will also have over 95% power to detect a greater than 15 second mean difference in physiological recovery (heart rate and oxygen saturation) between groups. In a recent study of skin-to-skin care [66], the time to return to baseline heart rate following the application of the plaster signifying the end of the procedure was significantly different, 123 seconds (*CI *103-142) for the Kangaroo Mother Care condition and 193 seconds for Incubator condition (*CI *158-227, *p *< .00001). Since all infants will receive 24% sucrose, we do not expect that the differences seen in time to recovery will be this large. Therefore, by using the larger sample, and conservatively accounting for the use of regression techniques, our study will recruit 128 participants (64 sets of twins, 32 assigned to the co-bedding group and 32 to the standard group).

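### Each coder scores only one arm, so a systematic scoring difference between the two coders biases the primary PIPP comparison, and the planned checks cannot remove it

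*Protocol article*

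**What the plan says.** The section on protecting against bias in the protocol article has video coding done "by 2 coders (coder A and coder B"), divided by arm: "Each coder will only code data on infants who are co-bedding (A) or code data on infants who are receiving standard care (B"). It presents the use of separate coders as a way to limit observer bias, and adds these safeguards:

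- Blinding: "The individuals coding pain response will be blinded to the twins treatment status (whether co-bedding or receiving standard care"). The camera shows only the face, coders stay off the unit, and they do not communicate with each other.
- Separate standardised training to an ICC of 0.85, with quarterly retests on standard tapes. Re-training and re-coding follow if the ICC falls below 0.75.
- Cross-coding after the study, in which the coders "code a random selection of approximately 20% (n = 6) of the tapes from the alternate group". Its purpose is stated as: "Inter-rater scores will be correlated to ensure that if differences are found between the groups, these differences are related to the intervention of co-bedding". The alternative it is meant to rule out is a consistent difference in how the coders score.

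The primary outcome is the pain response to heelstick: "Premature Infant Pain Profile (PIPP) scores) will be compared between co-bedding and standard care groups". The Sample Size section sets the target: "We designed the study to detect a difference of 1 point or greater change (SD 2.0) in the PIPP scores". The analysis section compares arm means before and after treatment, with GEE to allow for twin pairing.

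**The concern.** With one coder per arm, a difference in scoring habit cannot be told apart from a treatment difference in the main data. If coder A scores facial action more leniently than coder B, every co-bedded infant gets a lower score, whatever coder A knows about allocation. Had each coder scored part of each arm, the same difference would be mostly noise; this split turns it into bias.

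The target effect is only 1 PIPP point, so a modest difference in habit matters. It could produce a significant result with no benefit behind it, or hide a real benefit if it runs the other way. An analysis plan cannot repair this once coding is done: a coder covariate would be identical to the treatment indicator.

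**Working it through.** **Inputs.** From the Sample Size section: difference 1 point, SD 2.0, two-sided alpha 0.05, power 80%, 128 infants in 64 sets, 32 sets (64 infants) per arm. From the bias section: ICC 0.85 and 0.75, and n = 6 cross-coded tapes. Assumed, because the article does not give them: the size of the coder offset, the within-pair correlation, the ICC type (absolute agreement below) and the random coder error.

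**1. The plan's own figure.** The normal approximation gives 63 per arm (126 in all) and the t-test gives 63.8, so 64 per arm (128). Power at 64 per arm is 0.80 to 0.81. The stated 128 reproduces.

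**2. Effect of an offset b with no true effect.** The expected arm difference is b. SE = 2.0 × √(2/n_eff), with n_eff = 64/(1 + ρ) per arm for within-pair correlation ρ. P(reject) = 1 − Φ(1.96 − b/SE) + Φ(−1.96 − b/SE).

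| b (points) | ρ = 0 (n_eff 64) | ρ = 0.5 (n_eff 42.7) | ρ = 1 (n_eff 32) |
|---|---|---|---|
| 0 | 0.05 | 0.05 | 0.05 |
| 0.25 | 0.11 | 0.09 | 0.08 |
| 0.5 | 0.29 | 0.21 | 0.17 |
| 0.75 | 0.56 | 0.41 | 0.32 |
| 1.0 | 0.81 | 0.64 | 0.52 |

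The t-test gives about 0.80 and 0.50 at the two ends of the last row. If the true effect is 1 point and the offset is 0.5 point the other way, power falls from 0.81 to 0.29 (ρ = 0) or from 0.52 to 0.17 (ρ = 1).

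**3. Offset that the ICC limits allow.** For two fixed coders and absolute agreement, ICC = s²/(s² + e² + d²/2). Here s² is the true between-infant variance, e² the random coder error and d the offset, with s² + e² = 4.

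- Within-coder reliability 0.90 (s² = 3.6, e² = 0.4). ICC 0.85: d = √(2(3.6/0.85 − 4)) = 0.69. ICC 0.75: d = √(2(3.6/0.75 − 4)) = 1.26.
- Upper bounds with no random error (e² = 0). ICC 0.85: d = 1.19. ICC 0.75: d = 1.63.

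A consistency ICC would ignore a constant offset altogether.

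**4. The cross-coding check.** Scores 6, 8, 9, 10, 12, 13 and the same scores plus 1 have r = 1.0, so the correlation does not register a full-point offset. If the mean coder difference were computed instead, its 95% half-width would be t × SD_diff/√m for m double-coded tapes:

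| Random coder error | SD_diff | m = 6 | m = 12 |
|---|---|---|---|
| e² = 0.4 | √(2 × 0.4) = 0.89 | 0.94 | 0.57 |
| r = 0.85, all disagreement random | 2√(2 × 0.15) = 1.10 | 1.15 | 0.70 |
| r = 0.75, all disagreement random | 2√(2 × 0.25) = 1.41 | 1.48 | 0.90 |

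Even the best case, ±0.57, does not exclude a 0.5-point offset when the observed difference is zero.

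**5. Size of the subset.** 6/32 = 19%, so n = 6 fits about 20% of twin sets per arm. 6/64 = 9% of infants per arm; 20% of infants would be 12.8, about 13.

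**The case against.** The protocol sees the risk and does not ignore it: coders are blinded, trained to a common standard, retested quarterly and cross-checked at the end. Several stronger readings are tempting, and the article does not support them.

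- *No analysis could separate coder from arm.* True of the main data only. Double-coded tapes do estimate the coder difference. The fair criticism is that the estimate is imprecise and that the stated statistic is a correlation.
- *A 1-point offset could never be excluded.* This depends on reading n = 6 as the total. Six per coder, 12 in all, is a natural reading; the half-width is then 0.57 to 0.90, and an observed difference near zero would exclude 1 point.
- *The offset is 1.2 to 1.6 points.* Those are bounds that need zero random coder error, in which case a few tapes would show the offset exactly if the mean difference were examined. They must not be combined with intervals that assume all disagreement is random.
- *Any coder difference passes through one-for-one.* Random error adds only noise. Heart rate and oxygen saturation come from monitors and are probably less exposed. An offset identical at baseline and heelstick would cancel in a before/after contrast; one that grows with facial activity would not.
- *The n = 6 is an arithmetic error.* It matches twin sets.
- *Coders are easily unblinded.* That is conjecture, given face-only video and off-unit coding. Single-arm batches only make a breach more consequential, since learning the arm of one tape reveals the rest.

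The word for correlation may also be loose, since the other reliability checks use an ICC. All this narrows the point, but the arm-by-coder split and the bias it permits remain.

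**Conclusion.** The concern holds in this form: coder and arm are completely confounded in the main data, so a systematic coder difference in the coder-scored part of the PIPP at heelstick, net of whatever a baseline contrast cancels, biases the primary comparison. The safeguards may hint at such a difference but do not remove it. Offsets of about 0.7 and 1.3 points are compatible with the ICC limits at within-coder reliability 0.90 (upper bounds 1.2 and 1.6), and 6 to 12 tapes fix the mean difference only to about ±0.6 to ±1.5 points. With no true effect, type I error rises from 5% to about 17–29% for a 0.5-point offset and to about 50–80% for a 1-point offset, as within-pair correlation goes from 1 to 0. The offset sizes are assumptions: nothing in the article shows that the coders do differ.

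**What to change.** Allocate tapes at random to the two existing coders within arm and site, unlabelled, so that each scores about half of each arm, and balance both twins' recordings in the same way. Include coder as a covariate in the GEE model. Draw the double-coded subset from both arms and state whether 20% means twin sets (n = 6) or infants (about 13 per arm). Report the mean A-minus-B difference with its 95% CI and an absolute-agreement ICC in place of the correlation.

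With a balanced split, a constant offset contributes nothing to the expected arm difference. Even without a coder term, a 1-point offset would only raise the SD to √(4 + 0.25) = 2.06, with power about 0.78 against 0.81 for independent infants; with the term the loss is negligible. The sample size stays at 128.

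The cost is a changed allocation list, one model term and, if 20% of infants is chosen, 26 double-coded tapes: 14 more than 12 (six per coder), or 20 more if six in total was meant.
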